## Abstract

**Background:**

Prolonged sitting, an independent risk factor for disease development and premature mortality, is increasing in prevalence in high- and middle-income countries, with no signs of abating. Adults in such countries spend the largest proportion of their day in sedentary behaviour, most of which is accumulated at work. One promising method for reducing workplace sitting is the use of sit-stand desks. However, key uncertainties remain about this intervention, related to the quality of existing studies and a lack of focus on key outcomes, including energy expenditure. We are planning a randomised controlled trial to assess the impact of sit-stand desks at work on energy expenditure and sitting time in the short and longer term. To reduce the uncertainties related to the design of this trial, we propose a preliminary study to assess the feasibility and acceptability of the recruitment, allocation, measurement, retention and intervention procedures.

**Methods:**

Five hundred office-based employees from two companies in Cambridge, UK, will complete a survey to assess their interest in participating in a trial on the use of sit-stand desks at work. The workspaces of 100 of those interested in participating will be assessed for sit-stand desk installation suitability, and 20 participants will be randomised to either the use of sit-stand desks at work for 3 months or a waiting list control group. Energy expenditure and sitting time, measured via Actiheart and activPAL monitors, respectively, as well as cardio-metabolic and anthropometric outcomes and other outcomes relating to health and work performance, will be assessed in 10 randomly selected participants. All participants will also be interviewed about their experience of using the desks and participating in the study.

**Discussion:**

The findings are expected to inform the design of a trial assessing the impact of sit-stand desks at work on short and longer term workplace sitting, taking into account their impact on energy expenditure and the extent to which their use has compensation effects outside the workplace. The findings from such a trial are expected to inform discussions regarding the potential of sit-stand desks at work to alleviate the harm to cardio-metabolic health arising from prolonged sitting.

**Trial registration:**

ISRCTN44827407

## Background

Recent years have witnessed an increased awareness of the detrimental effects of sedentary behaviour (i.e. any waking behaviour characterised by low energy expenditure (≤1.5 METs) and low muscle contraction levels, while sitting or reclining [1–3]). Prolonged sitting time has been shown to increase the risk of obesity, weight gain, diabetes, some cancers, cardiovascular disease and premature mortality, as well as mental health problems [4–9]. These effects are generally shown to be independent of the amount of time spent in moderate-to-vigorous physical activity [1, 10–18]. This implies that one could meet or exceed the recommended daily physical activity levels but still be at risk if the rest of the day is spent sitting. Sedentary behaviour accumulated in prolonged uninterrupted bouts (e.g. bouts >30 min) is considered especially problematic, being associated with less healthy cardio-metabolic profiles compared to interrupted sitting, independent of total sitting time [19–22]. The time spent in sedentary behaviour is increasing rapidly on a global scale [23–26] and is expected to continue to do so without intervention [23], rendering it a critical target for public health action [27].

Working-age adults in high-income countries spend approximately 8–9 h a day in sedentary behaviour [28, 29], which is mainly accumulated in three domains: the workplace, at home during leisure, and transport [30]. The majority of all sitting time, however, is gathered at work [31]. Indeed, jobs are becoming increasingly less active and more sedentary [32], with working adults spending often more than two thirds of their time at work sitting [31, 33, 34]. Not only are office workers sedentary most of their time at work, they also tend to sit for prolonged, uninterrupted periods of time. Of further concern is that those who are sedentary for a large proportion of their working day do not compensate by increasing their physical activity levels and/or reducing their sedentary behaviour during leisure time [31, 35, 36]. Reducing and/or breaking up sitting time at work could substantially attenuate the risk of metabolic and cardiovascular disease among office workers [19, 20]. Given that office workers are one of the largest occupational groups [37, 38], decreasing their sedentary behaviour could have impactful population health benefits, making them an important target for preventative approaches [2, 29]. In line with this, recently published expert guidelines advise those working in desk-based occupations to increase standing time and light activity at work by 2–4 h a day [39], although the quality of the evidence that has led to these recommendations is generally low and caution has been advised to policymakers about issuing guidance regarding sitting time reductions as a stand-alone public health intervention [40].

In the past, most existing work-based interventions had focused on increasing levels of physical activity [29, 30]. In recent years, however, there has been a marked interest in identifying ways to reduce occupational sedentary time and promote breaks in sitting. One promising intervention is to alter the workplace environment by providing adjustable sit-stand desks, which allow individuals to work in sitting or standing positions [41]. The occupational ergonomics literature has focused on sit-stand desks for decades [42–44] and has shown that their use can decrease musculoskeletal discomfort without affecting (and sometimes even increasing) work productivity [43, 45–50]. Recently, the use of such desks for reducing prolonged workplace sitting has received new interest, with a number of studies attempting to assess their effectiveness [27, 45, 51–61]. Most of these suggest that installation of sit-stand desks can lead to reduced workplace sitting time and increased standing [27, 51, 52, 54–57, 62–64] (for reviews, see Torbeys et al. (2014) [65] and Neuhaus et al. (2014) [66]), although a couple have failed to find similar effects [53, 60]. One study also reported improvements to high-density lipoprotein (HDL) cholesterol [51] with the use of such desks. However, as concluded by recent reviews [41, 67, 68], the quality of the relevant evidence is low due to most studies’ reliance on small sample sizes and use of low-quality research designs, including the lack of randomisation.

A small number of relevant randomised trials have been conducted [45, 54, 57–59, 61, 62, 69], which, although provide valuable information regarding the use of sit-stand desks work, have some critical limitations leaving key uncertainties regarding the intervention’s impact on sedentary behaviour. These arise from unreliable measurement of sedentary behaviour, weak study designs and lack of consideration of wider behavioural effects of sit-stand desks. For example, some existing trials have used measures of sedentary time that are subjective [45, 62], inadequately validated [54] or unable to distinguish activity in different postures (i.e. sitting vs standing) [54, 58]. Furthermore, results from some trials do not allow observed effects to be attributed to sit-stand desks due to the use of multicomponent interventions [59, 61, 64] or presence of possible confounders. For example, in one trial participants were informed of and reminded weekly of the intervention’s goal to replace 50 % of workplace sitting with standing. Having this knowledge and receiving these weekly prompts could have influenced sitting time thus confounding the impact of sit-stand desks [54]. In addition, reliable estimates of the potential for sit-stand desks to have compensation effects, i.e. greater non-working sitting time and lower energy expenditure and/or increased energy consumption from food and drinks, are precluded by methodological limitations in the few studies that have examined this. These include the use of subjective [57] or invalidated measures to assess sedentary behaviour outside the workplace [54].

Importantly, none of the existing trials have assessed key outcomes relevant to the use of sit-stand desks at work. The first of these includes energy expenditure. Recently, sit-stand desks have been marketed as a means to burn more calories, with alleged benefits to weight loss. However, as pointed out in the aforementioned expert guidelines [39] and confirmed by a recent systematic review of the impact of sit-stand on health-related outcomes, including energy expenditure [70], the existing evidence for such claims is equivocal. The few studies that have assessed energy expenditure in adults with the use of sit-stand desks (for review, see Tudor-Locke et al. (2013) [71]) have been conducted in the laboratory, with small sample sizes, over short periods of time and not part of interventions to reduce sitting. The use of sit-stand desks in the workplace could potentially encourage increased movement, as well as standing during non-working hours. They could also, however, lead to decreased activity during non-work hours (i.e. compensatory behaviour) due to possible fatigue arising from increased standing at work. Such effects cannot be captured in short-duration laboratory-based studies. Quantifying precisely the potential size of the impact of using sit-stand desks at work on overall energy expenditure—in addition to workplace sitting time changes which might have acute physiological effects independent of energy balance—is essential to gauge whether the intervention is likely to have cardio-metabolic health impacts in the short and longer term. It would also allow assessment of ‘compensatory behaviour’.

The second key outcome not assessed by most existing trials is the impact of sit-stand desks on longer term sedentary behaviour. Inclusion of longer term assessments is essential for estimating the sustainability of any observed benefits [66]. Only one trial, currently being conducted, has planned long-term assessments [69]. However, the proposed sample size of this trial is very small (30 participants; 10 participants in each group, which might be further reduced by the potential attrition rates at the longest follow-up assessment). Hence, the quality of the evidence generated by this study is expected to be limited.

In addition, most existing trials (apart from the study by Dunstan et al. (2013) [59], which assessed a multicomponent intervention) have not measured outcomes related to health and cardio-metabolic profiles, which are necessary for the precise evaluation of the potential health benefits of using sit-stand desks at work [29]. Indeed, it was recently concluded that there are substantial evidence gaps to allow for an understanding of the potential of such desks to enhance cardiovascular health benefits by reducing sedentary time [70].

Finally, it is currently unknown whether the potential effects of sit-stand desks on sitting time depend on users’ socio-economic status and therefore the potential for such desks to reduce or increase health inequalities. Although relevant studies are scarce, there is some evidence to suggest that sedentary behaviour is socially patterned. For example, higher levels of TV-viewing have been associated with lower socio-economic status [72, 73] while higher workplace sitting time is associated with higher socio-economic status [73, 74]. We note, however, that existing studies have not focused on the impact of socio-economic status on sitting time specifically among office-based employees. There is a need to determine whether sit-stand desks have the potential to reduce any differences in sitting time arising as a function of socio-economic position among office-based employees and in turn whether they can help reduce the health inequalities that potentially follow from these differences.

We are planning a randomised controlled trial to address the aforementioned uncertainties and extend current knowledge regarding the effectiveness of sit-stand desks at work in reducing overall sedentary behaviour. The planned trial will assess the impact of sit-stand desks at work on energy expenditure and sitting time in the short and longer term, while incorporating a more robust research design than existing studies, including a large sample size and a more valid and reliable measure of the time spent in different body postures. It will also include an assessment of key cardio-metabolic outcomes and will assess whether any effects of sit-stand desks on sitting time are modified by socio-demographic variables, including users’ socio-economic status.

Prior to conducting the aforementioned trial, there is a need to reduce key uncertainties related to its design. These include the following: (i) the feasibility of recruiting eligible participants; (ii) the feasibility of delivering the intervention to participants, i.e. of installing sit-stand desks in their workspaces; (iii) the practical issues associated with delivering the intervention, including the suitability of workspaces for desk installation (e.g. dimensions of available space and room/furniture configuration) and the potential need for storage space for existing and acquired desks; (iv) the number of each desk type^1^ needed for the trial, which depends on potential participants’ preferences for desk mounts vs full desks, as well as the match between their preferences and workspace suitability; and (v) participants’ acceptability of sit-stand desks. To reduce these uncertainties, we are initially proposing a preliminary study with the aim of assessing the feasibility of the procedures for recruitment, measurement, and intervention delivery of the aforementioned randomised controlled trial.

### Aim and objectives

The aim of the current study is to assess the feasibility of conducting a randomised controlled trial of the impact of sit-stand desks at work on energy expenditure and sedentary time. The specific objectives of the study are to:Assess the feasibility of recruiting eligible participants into the trial, by estimating and describing:(i)The proportion of eligible participants who are interested in taking part in the trial(ii)The baseline characteristics of eligible participants who are interested in participating in the trial, to judge the likelihood of recruiting a sample varied in the potential effect modifiers of interest (BMI, SES, age, gender)(iii)The expected recruitment rate(iv)The number of recruitment sites (organisations) needed to achieve the target sample size for the main trial
Estimate the number of desk mounts and full desks needed for the main trial, by describing:(i)The proportion of eligible participants preferring desk mounts vs full desks(ii)The proportion of eligible participants with workspaces that permit installation of their desk preference
Explore people’s preference regarding the location for the baseline and follow-up assessments (home vs workplace vs clinical research facility)Assess the feasibility and practicalities associated with delivering the intervention (i.e. installing the sit-stand desks)Explore the circumstances under which desks are used in standing mode and the factors that affect desk useEstimate retention and loss to follow-up ratesExplore the acceptability of the interventionExplore the acceptability of the outcome assessments and study proceduresAssess the variability of outcomes, to inform sample size calculations for the planned trial

## Methods

### Setting and context

The proposed feasibility study will be conducted within two organisations. The first is the Cambridge University Hospitals, National Health Service (NHS) Foundation Trust^2^, which includes two hospitals in Cambridge, UK: Addenbrooke’s Hospital and The Rosie Hospital.

The NHS is one of the largest employers in the world and is the biggest in Europe, with over 1.6 million staff [75]. The cost to the NHS of staff absence due to poor health has been estimated to be £2.4 billion a year. In September 2015, the Chief Executive of NHS England announced a major drive to improve the health and wellbeing of health service staff, which includes initiatives aimed at establishing and promoting physical activity [76].

The second organisation is a private genomics company that specialises in the development, manufacturing and marketing of integrated systems for the analysis of genetic variation and biological function. The company’s headquarters are in the USA but have recently branched out into Cambridge, UK, where approximately 500 employees work across three sites. The study will be conducted in one of the three sites where most office-based employees are based.

## Design

The proposed feasibility study will consist of four phases (phases I–IV) (Fig. 1). Each phase will address different aims and employ a variety of methods for doing so, including:A survey (phase I)Workspace auditing (phase II)A cross-over randomised component (phase III)Direct observations (phase III)Qualitative interviews (phase IV)

**Fig. 1 Fig1:**
[figure not shown]
Study overview and participant flow

### Participants

Participants will be office-based employees of two companies in Cambridge, UK.

#### Inclusion criteria

Work at least 0.6 full-timeSpend at least 70 % of a working week performing desk-related activities

#### Exclusion criteria

Are already using sit-stand desksDo not have use of their own personal deskHave musculoskeletal disorders that make prolonged standing inadvisableHave chronic illnesses that prevent prolonged periods of standingAre planning to be absent from the workplace for more than 14 working days during the study periodAre pregnant

For phase I, 500 eligible employees will be targeted. Phase II will involve 100 participants. Both phases III and IV will involve 20 participants.

Eligible participants will be identified and recruited through (i) employment databases and invited via letter/email and (ii) adverts in local newsletters and flyers posted within the buildings of target organisations.

### Sample size

No formal sample size calculations are produced for this feasibility study. Sample sizes for each phase (see Fig. 1) are chosen based on resources. However, it is possible to determine the precision with which certain parameters can be estimated with the sample sizes chosen for each of the study phases.

To achieve the target of 500 individuals completing phase I, the survey will be circulated to approximately 1400 individuals. Although in organisational research the average response rate from individual respondents is 53 %, we have based our estimate on the conservative expected rate of 35 %, which is the average survey response rate for organisational respondents [77–79].

Based on the average interest rates reported in previous studies assessing the impact of sit-stand desks on sitting time, the expected proportion of participants interested in taking part in a trial of sit-stand desks at work is 37 %. With 500 participants, the 95 % confidence intervals around an estimate of 37 % would be from 33 to 41 %.

Based on the average recruitment rates reported in previous studies assessing the impact of sit-stand desks on sitting time, the expected recruitment rate is 33 %. With 500 participants, the 95 % confidence intervals around an estimate of 33 % would be from 29 to 37 %.

The average attrition rate between baseline and follow-up reported in previous studies assessing the impact of sit-stand desks is 10 %. With 20 participants, the 95 % confidence intervals around an estimate of 10 % would be from 2 to 33 %. The maximum attrition rate reported in previous relevant studies is 14 %. With 20 participants, the 95 % confidence intervals around an estimate of 14 % would be from 3.5 to 38 %.

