### Procedure

#### Phase I

During phase I, approximately 1400 eligible participants from across organisations will be invited to complete an online survey, of whom we aim 500 to complete the survey, to assess the following: (a) their interest in participating in a trial aiming to assess the use of sit-stand desks at work; (b) their preferences for different desk types (full desks vs desk mounts); and (c) their preference regarding the location (home vs workplace vs clinical research facility) for the baseline and follow-up assessments.

The survey will include a brief description of the trial and will ask people to indicate their willingness to participate, via a yes/no response. The proposed duration of the future full trial, the design of which this feasibility study aims to clarify, is 6 months, Due to resource restrictions, the duration of the randomised component of the proposed feasibility study will be 3 months. To gauge any potential differences in interest to participate as a function of the trial duration, all participants will be asked to respond to two relevant questions: one enquiring about their interest in a trial lasting 3 months and one enquiring about their interest in a trial lasting 6 months. The order in which these questions appear will be randomised. Participants will also be asked to indicate their preference regarding potential locations for the assessments to take place (home, workplace, or clinical research facility).

The survey will also include a brief description, with pictures, of the two different types of sit-stand desks available: full desks and desk mounts that are installed on top of existing desks. Links to videos demonstrating how each desk type works will also be provided.

The survey will also include questions relevant to participants’ demographic information, including age, gender, level of education, BMI, smoking status, salary band, and position within the organisation.

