#### Phase II

Of the participants indicating an interest in taking part in the trial during phase I, 100 chosen at random will be visited by a researcher who will assess their workspaces for desk installation suitability. To do this, the researcher will measure the following: (a) the dimensions of the workspace, (b) the dimensions of existing desks, and (c) the dimensions of any available (empty) space. The researcher will also record (through photographs and notes) the configuration of the space (i.e. shape of the room) and of the furniture within that space, making note of any obstacles that might inhibit desk installation and/or use (e.g. shelves that would obstruct sit-stand desks being put into standing mode).

These measurements and records will be compared against measurements involving the space and room configurations needed to successfully install each desk type, identified from measuring acquired samples of each desk type.

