#### Phase III

Twenty randomly selected participants of those whose workspaces will be measured during phase II will be randomised to either the use of sit-stand desks (full desks or desk mounts depending on their preference and workspace limitations) at work for 3 months or a waiting list control group. Those allocated to the waiting list control group will continue using their existing desks and will be offered sit-stand desks 3 months later.

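### The 29 to 37 % interval for the recruitment rate rests on 500 survey respondents, but the design can observe uptake only among the few people invited to the randomised phase

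*Protocol article*

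**What the plan says.** The Sample size section of the protocol article makes no formal calculation. Instead it gives the precision that the chosen phase sizes allow.

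- **Origin of the 500.** They are phase I survey completers: "To achieve the target of 500 individuals completing phase I, the survey will be circulated to approximately 1400 individuals".
- **Interest.** The expected value is 37 %, and "With 500 participants, the 95 % confidence intervals around an estimate of 37 % would be from 33 to 41" %.
- **Recruitment.** The section says "the expected recruitment rate is 33" %, and then "With 500 participants, the 95 % confidence intervals around an estimate of 33 % would be from 29 to 37" %.
- **Attrition.** This is sized on 20 participants, the number randomised.

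The Procedure section describes the phases:

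- **Phase I.** The survey "will ask people to indicate their willingness to participate, via a yes/no response".
- **Phase II.** Of those who say they are interested, "100 chosen at random will be visited by a researcher who will assess their workspaces for desk installation suitability".
- **Phase III.** "Twenty randomly selected participants of those whose workspaces will be measured during phase II will be randomised".

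Aim and objectives lists the proportion interested and the expected recruitment rate as separate items, followed by the number of organisations needed for the main trial. Data analysis includes recruitment rates among the main descriptive results. The article does not define the numerator or denominator of the recruitment rate.

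**The concern.** Interest and recruitment have different expected values and are different objectives, yet both are given a precision on the same 500 people. All 500 answer the interest question. Most of them are never offered a place: the researchers choose 100 for the workspace visit and 20 of those for randomisation, and resources fix both numbers. A survey answer therefore cannot supply the recruitment rate, and the two later phases are too small to supply it on a base of 500.

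The recruitment rate bears on how many organisations the main trial will need. If stated willingness is reported as recruitment, or if a projected rate is quoted to within 4 points when the data support less, that number of sites could be set with too much confidence.

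**Working it through.** **Inputs.** Interest 37 %, recruitment 33 % and 500 survey completers (Sample size); 100 visited (Phase II); 20 randomised (Phase III). The number invited to phase III is not stated and is assumed below.

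**1. Reproduce the stated interval.** For one proportion, p ± 1.96 × √[p(1 − p)/n]:

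√(0.33 × 0.67 / 500) = 0.0210, and 1.96 × 0.0210 = 0.041, so the interval is 28.9 to 37.1 %.

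Wilson (29.0 to 37.2 %), continuity-corrected Wilson (28.9 to 37.3 %) and exact (28.9 to 37.3 %) intervals all round to 29 to 37 %. The continuity-corrected Wilson method also reproduces the attrition interval for 10 % of 20 (1.8 to 33.1 %). The calculation is sound; the question is what n should be.

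**2. Compare with the design.** 0.33 × 500 = 165 recruits. That is more than the 100 visited and more than eight times the 20 places (165 / 20 = 8.25). The ratio 20/100 does not help either, because the researchers fix both numbers.

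**3. Reading A: 33 % and 37 % share the base of survey completers.** Implied uptake among the interested is 0.33 / 0.37 = 0.892. Filling 20 places then takes about 20 / 0.892 ≈ 22 invitations. Ignoring workspace losses, the overall rate is p₁p₂, with p₁ = 0.37 (n₁ = 500) and p₂ = 0.892 (n₂ = 22). By the delta method:

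SE = p₁p₂ × √[(1 − p₁)/(n₁p₁) + (1 − p₂)/(n₂p₂)]

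= 0.33 × √[0.63/185 + 0.108/19.6] = 0.33 × √(0.00341 + 0.00551) = 0.0312

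1.96 × 0.0312 = 0.061, so the interval is 26.9 to 39.1 %. The half-width of 6.1 points is about 1.5 times the stated 4.1.

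Keeping only the interest term gives 1.96 × 0.33 × √0.00341 = 0.038, or 29.2 to 36.8 %. On this reading the published interval is about what results from treating uptake as known.

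**4. Reading B: 33 % is the uptake among already-interested invitees.** Then 20 / 0.33 ≈ 60 invitations fill 20 places. The exact interval for 20/60 is 21.7 to 46.7 %. The half-width of 12.5 points is about 3 times the stated one.

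**5. Sensitivity to the number invited.** If all 100 visited people were asked to consent and uptake were 89 %, reading A with n₂ = 100 gives 0.33 × √(0.00341 + 0.00121) = 0.0224 and an interval of 28.6 to 37.4 %, still ignoring workspace losses. That is close to the stated precision, but the article describes no such step.

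The delta-method figures are approximate, because 22 invitations is a small number.

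**The case against.** **The arithmetic is right.** This stands in full. A reader might infer a calculation error; there is none.

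**The rate may be a projection for the main trial.** The objective speaks of an expected rate, and such a projection can properly use the 500 survey answers. This partly stands. A reader might infer that the plan intends to report 20/500 = 4 %, but nothing in the article says so, and the comparison with 20 places shows only that the rate cannot be observed directly on that base. A projection must still carry the uncertainty of the later steps, and an interval on n = 500 alone does not. If the projection were stated willingness alone, it would be the interest rate again, which has its own objective and a different expected value.

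**A threefold understatement is not established.** This stands as a limit on size. Reading B applies 33 % to people who have already said they are interested. The article does not say that its 33 % has that meaning, and on the shared-base reading the understatement is about 1.5 times.

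**Parts of the recruitment funnel are already planned.** Interest, workspace suitability and drop-out between phases are listed outcomes, the flow figure is not shown, and an article may leave a log to the full protocol. That is fair, and the absence of a log is no fault in itself. The fault is a published figure whose denominator conflicts with the design described beside it.

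**Conclusion.** The concern holds as a wrong denominator for a stated precision. The 500 survey completers support the 37 % interest rate and its interval. They do not support 29 to 37 % for recruitment, which also depends on workspace suitability and on uptake among the people actually invited.

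The understatement is roughly 1.5 to 3 times in half-width: about 27 to 39 % on the shared-base reading and about 22 to 47 % on the conditional-uptake reading. Both figures assume that invitations stop when 20 places are filled. The first also ignores workspace losses; the second is a precision for uptake, not for the overall rate. Inviting many more people would narrow the gap.

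Severity is moderate. Phase sizes were set by resources and no test uses the interval, so the effect falls on planning the number of sites for the main trial.

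**What to change.** 1. Withdraw the 29 to 37 % statement, or relabel it as a survey-based projection that omits later-stage uncertainty.
2. Define uptake as the number consenting divided by the number invited to phase III, and keep a simple log of invitations and answers.
3. Estimate the overall recruitment rate, and from it the number of sites, as interest × workspace suitability × uptake. Give it an interval that carries the uncertainty of all three. Uptake alone will not do, because invitees have already been screened for interest.
4. State the expected precision as a range with its assumptions: about 27 to 39 % if 33 % is 37 % interest times about 89 % uptake among about 22 invited, ignoring suitability losses; about 22 to 47 % only if 33 % is the uptake among about 60 already-interested invitees. Replace the range once the number to be invited is fixed.

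The cost is a change of wording, a short log and a less favourable stated precision. No phase size changes and no procedure is added for participants.
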